### Fundamental Frequency

We derive fundamental frequency (f_0_) mean from the couple conversations as a marker of expressed emotional arousal during the interaction for each dyad member. Audio recordings are made using Lavalier microphones (Shure BLX88 and Tascam DR-40 Linear PCM recorder), with each microphone targeting one dyad member and recording onto a separate channel, resulting in relative differences in volume depending on who is speaking at a given time. We then extract f_0_ as a continuous measure across the 15-min conversation in estimated values (hertz, Hz) for every quarter-second using Praat (Boersma and Weenink, 2019), with a bandpass filter of 75–300 Hz to restrict values to the normal range of adult speech (Owren and Bachorowski, 2007; Weusthoff et al., 2013). We also extract intensity in decibel (dB) for every quarter-second to identify patient and partner speech (procedures similar to Bryan et al., 2018). Speaker changes (marking talk turns) are identified based on zero-crossover points in intensity values between the two channels and a minimum threshold of intensity differences observed *via* visual inspection of the intensity plots. Instances of overlapping speech or external background noises result in subthreshold difference scores and are removed during this procedure. Where speaker diarization is not possible using this procedure, speaker tracks are manually segmented using Audacity (Team, 2018). f_0_ mean values are then aggregated at each talk turn (time when one person speaks before the other partner begins speaking); plots are visually inspected for outliers, and observations are removed as needed (e.g., not previously identified background noises or overlaps in speech, non-speech vocalizations). All data management procedures are conducted using Stata 16 (StataCorp, 2021).

### Incentives

Participants can earn up to $200 per person or $400 per couple for completing all parts of the study. Table 5 displays payment amounts per study activity.

**TABLE 5 T5:** Incentives as a function of study activity.

Activity	Payment per individual	Payment per dyad
Laboratory visit	$50	$100
Ecological momentary assessment	$75 if completed at least 85% of assessments, otherwise $3 per assessment	$150
Follow-up questionnaires	$75 ($25 per assessment × 3)	$150
Total	$200	$400

### COVID Considerations

The first participants were enrolled in May of 2017. When in-person activities with human subjects were restricted due to the SARS-CoV-2 pandemic in March of 2020, we moved to IRB-approved remote enrollment. This allowed us to continue to carry out all study activities with the exception of the in-person couple conversation. The consent process was conducted *via* telephone and participants signed the consent form electronically through REDCap.

### Data Analysis

#### Sample Size and Power

We project a complete-case sample of approximately 264 dyads for the questionnaire portion of the study, in other words, 264 dyads for which *both* members complete T1, T2, T3, *and* T4 questionnaires. This is based on anticipated numbers of patients meeting medical recruitment criteria at each site as well as estimates regarding: the proportion of patients married or in committed cohabiting partnerships (80%), the proportion of patient-partner dyads agreeing to participate (50%), disease-specific survival rates, and drop-out over time (30%). Based on power calculations for indirect effects (Vittinghoff and Neilands, 2015) conducted in NCSS/PASS version 2021, this sample size (264 retained from 434 enrolled) should afford power of 0.80 to detect indirect (mediated) associations of communication measures (Xs) with outcomes (Ys; relationship satisfaction and psychological distress) *via* measures of cognitive processing and intimacy (Ms) comprising small-to-moderate constituent (i.e., X→M and M→Y) associations of *r* ≥ 0.25, assuming moderate confounding of X→M and M→Y associations (*R*^2^ = 0.15).

### Overview

Associations hypothesized under the SCP and RI models will be examined with structural equation models (SEMs) separately for questionnaire data from T1-T4 and data from the EMA phase, primarily in a longitudinal actor-partner interdependence model (APIM) framework, with patients and partners treated as distinguishable dyad members (Ledermann et al., 2011). To examine longitudinal within-couple associations in the questionnaire data, random intercept cross-lagged panel models (Hamaker et al., 2015) will be estimated. EMA data will be analyzed using multilevel SEMs with repeated observations of patient- and partner-reported measures treated as being nested within dyads. Differences in hypothesized associations based on gender and role (patient vs. partner) will be examined using a variety of dyadic and non-dyadic analytic approaches as detailed below. Examination of how different assessments of communication (questionnaire, EMA, and objective assessment) prospectively predict psychological and relationship adjustment at follow-up will also be estimated using SEMs in an APIM framework.

All SEMs will be estimated in Mplus 8.7. Bootstrap standard errors for direct and indirect effects will be estimated, except for multilevel SEMs, where a Monte Carlo simulation approach will be used (see, e.g., Zyphur et al., 2016). For models that prove to be unestimable under maximum likelihood (ML) estimation (e.g., due to computational demands of numerical integration), Bayseian estimation will be used. Models fit using ML will be evaluated using comparative fit index (CFI), root mean squared error of approximation (RMSEA), and standardized root mean square residual (SRMR) values, with CFI > 0.95, RMSEA ≤ 0.06 (with upper confidence limit ≤ 0.08), and SRMR < 0.08 as benchmarks for acceptable model fit (Hu and Bentler, 1999). For models fit using the Bayes estimator, Bayesian versions of CFI and RMSEA values (Asparouhov and Muthen, 2021) will be examined.

#### Preliminary Analyses

Prior to conducting the primary analyses, we will use univariate and bivariate statistics and plots to examine distributions of, and associations among, key study variables. The reliability of each multi-item composite measure in the questionnaire data will be evaluated using Cronbach’s alpha, and reliability of composite measures from the EMA data will be evaluated using methods described by Cranford et al. (2006).

#### Examining Social-Cognitive Processing and Relationship Intimacy Models

##### Questionnaire Data

To examine the overall fit of the SCP model and the RI model in explaining patient and partner psychological and relationship adjustment over the course of 1 year using T1-T4 questionnaire data, we will use structural equation models (SEMs) within an APIM framework, in which measures from both dyad members (i.e., patient and partner) are included in each analysis. In these SEMs, a proposed latent factor with 6 indicators (scale scores for the questionnaire measures of holding back, disclosure, perceived constraints, enacted and received protective buffering, and constructive communication) reflecting overall communication will prospectively predict either a cognitive processing (avoidance and intrusive thoughts) composite (under the SCP model) or intimacy (under the RI model), which will, in turn, prospectively predict measures of psychological distress (POMS Total Mood Disturbance [TMD] or CESD score) and relationship adjustment (DAS total score). Prior to estimating the full SEMs for the questionnaire data, a measurement model for the proposed communication factor will be developed and refined using a confirmatory factor analysis approach. The degree of measurement invariance (e.g., configural vs. metric vs. scalar) for this proposed latent factor between patients and partners (and between men and women) will be evaluated in a sequential fashion. Non-invariance at each step in the sequence will be assessed using likelihood ratio tests (with α = 0.05) and changes in CFI (target ≤ 0.01). Potential sources of non-invariance (e.g., unequal loadings) will be investigated and the measurement model will be modified accordingly (e.g., dropping non-invariant indicators).

In line with the general APIM framework, both prospective actor (within-person, cross-construct) effects (e.g., *patient* communication predicting *patient* intimacy) and prospective partner (between-person, cross-construct) effects (e.g., *patient* communication predicting *partner* intimacy) will be estimated along with autoregressive (prospective within-person, within-construct) associations. Mediators and outcomes will be treated as manifest variables in these models. Latent person-level intercept factors will be included to account for random between-person variability in mean levels of model constructs. Within-couple indirect associations of communication and outcomes (psychological distress or relationship adjustment) *via* mediators (e.g., actor-actor effects and partner-actor effects) will be estimated using a product-of-coefficients approach (MacKinnon et al., 2007) and evaluated using 95% confidence intervals.

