## Abstract

Cancer and its treatment pose challenges that affect not only patients but also their significant others, including intimate partners. Accumulating evidence suggests that couples’ ability to communicate effectively plays a major role in the psychological adjustment of both individuals and the quality of their relationship. Two key conceptual models have been proposed to account for how couple communication impacts psychological and relationship adjustment: the social-cognitive processing (SCP) model and the relationship intimacy (RI) model. These models posit different mechanisms and outcomes, and thus have different implications for intervention. The purpose of this project is to test and compare the utility of these models using comprehensive and methodologically rigorous methods. Aims are: (1) to examine the overall fit of the SCP and RI models in explaining patient and partner psychological and relationship adjustment as they occur on a day-to-day basis and over the course of 1 year; (2) to examine the fit of the models for different subgroups (males vs. females, and patients vs. partners); and (3) to examine the utility of various methods of assessing communication by examining the degree to which baseline indices from different measurement strategies predict self-reported adjustment at 1-year follow up. The study employs a longitudinal, multi-method approach to examining communication processes including: standard self-report questionnaires assessing process and outcome variables collected quarterly over the course of 1 year; smartphone-based ecological momentary assessments to sample participant reports in real time; and laboratory-based couple conversations from which we derive observational measures of communicative behavior and affective expression, as well as vocal indices of emotional arousal. Participants are patients with stage II-IV breast, colon, rectal, or lung cancer and their spouses/partners, recruited from two NCI-designated comprehensive cancer centers. Results will be published in scientific journals, presented at scientific conferences, and conveyed to a larger audience through infographics and social media outlets. Findings will inform theory, measurement, and the design and implementation of efficacious interventions aimed at optimizing both patient and partner well-being.

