We hypothesize that the SCP model will predict individual psychological adjustment *via* actor effects, and that the RI model will predict individual psychological adjustment *via* actor effects and relationship adjustment *via* both actor and partner effects (aim 1). It is also likely that the strength of these associations will vary between individuals or subgroups (aim 2). While there are numerous variables that could potentially moderate these mediating effects, based on the literature and potential clinical relevance, we chose to examine gender and role (patient vs. spouse). With regard to gender, stronger positive associations between perceived social constraints and distress have been found among male vs. female cancer patients (Zakowski et al., 2003). Further, females report discussing their cancer with a wider circle of confidantes than do males (Harrison et al., 1995) which could result in increased cognitive processing of their cancer experience outside the relationship. Thus, lack of cognitive processing may be a more important driver of distress for males vs. females. With regard to role, patients and partners often have different assumptions about how they should support each other, with some partners believing that it is harmful for the patient to discuss their cancer or any negative aspects of the situation (Peters-Golden, 1982); this is reflected in findings that partners report higher levels of protective buffering than do patients (Langer et al., 2009). Thus, it is possible that the negative effects of such buffering may be experienced more by patients than by partners, but this requires further examination. Regarding aim 3, because EMA and objective measures are less subject to reporting biases (e.g., social desirability and recall), we hypothesize that they will better predict outcomes.

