##### Ecological Momentary Assessment Data

The EMA dataset will be structured with study days (level 1 units) nested within couples (level 2 units). Each study day observation will have values for patient and partner reports of afternoon communication (holding back, disclosure, protective buffering, support, perceived partner holding back, perceived partner support) as exogenous predictors, afternoon reports of cognitive processing (avoidance, intrusive thoughts) or intimacy as mediators, and evening reports of psychological distress (POMS TMD composite) or relationship satisfaction as outcomes, all from the same day’s afternoon and evening assessments. In addition, autoregressive associations are included such that afternoon reports of mediators are predicted from the preceding evening’s reports of the same variables (e.g., patient evening report of intimacy on day t-1 predicts patient afternoon report of intimacy on day t) and each evening outcome variable is predicted by the immediately preceding observation on the same variable. See Figure 2 for an example treating intimacy as the mediator and distress as the criterion, with variables and paths of conceptual interest in black, and control variables and paths less central to the conceptual models in gray. Indirect associations of afternoon communication with change in same-day evening outcomes (distress or relationship satisfaction) *via* mediators assessed on that same afternoon will be estimated using a product-of-coefficients approach and evaluated using 95% confidence intervals.

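### The comparison of the SCP and RI models is not met by the analysis as specified: each mediator is tested only with its rival left out, which matters most for psychological distress

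*Protocol article*

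**What the plan says.** The Abstract gives the aim in these words: "The purpose of this project is to test and compare the utility of these models using comprehensive and methodologically rigorous methods". The Discussion then draws contrasting implications for intervention from support for one model or the other.

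The article does state the mediator specification:

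- **Questionnaire data.** The communication factor "will prospectively predict either a cognitive processing (avoidance and intrusive thoughts) composite (under the SCP model) or intimacy (under the RI model". The mediator in turn predicts distress and relationship adjustment.
- **EMA data.** The models use "afternoon reports of cognitive processing (avoidance, intrusive thoughts) or intimacy as mediators", and the illustration is a one-mechanism model: "See Figure 2 for an example treating intimacy as the mediator and distress as the criterion".
- **Test of mediation.** In both data sets the indirect effect is a product of coefficients, judged by a 95% confidence interval.
- **Fit.** The Overview sets absolute cut-offs for models fitted by maximum likelihood, "with CFI > 0.95, RMSEA ≤ 0.06 (with upper confidence limit ≤ 0.08), and SRMR < 0.08 as benchmarks for acceptable model fit".

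The Introduction hypothesises that SCP predicts psychological adjustment through actor effects, and that "the RI model will predict individual psychological adjustment *via* actor effects and relationship adjustment *via* both actor and partner effects". Psychological adjustment is therefore assigned to both theories.

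**The concern.** Cognitive processing and intimacy are rival explanations of how communication reaches the same outcome. When each is tested without the other, an apparent effect of one may be borrowed from the other. Suppose communication moves both mediators, only intimacy acts on distress, and the two share variance that communication does not explain. The SCP model then attributes part of intimacy's effect to cognitive processing. The same holds with the roles reversed.

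The Introduction makes this scenario plausible. It reports moderately strong associations of social constraints with intrusive thoughts and with distress, but little evidence that cognitive processing is the mediator.

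Two separate intervals, each excluding zero, would be reported as support for both theories. They would not show whether both mechanisms operate or only one. The Discussion rests its choice of intervention focus on that answer. By contrast, the section on gender and role specifies interaction terms, equality constraints and tests of between-role differences in indirect effects. The SCP-versus-RI comparison has no counterpart.

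**Working it through.** **1. The plan's own power figure.** Sample Size and Power states 264 complete dyads, both constituent correlations at least 0.25, confounding R² = 0.15 and power 0.80. A joint-significance calculation at two-sided 0.05 (alpha is not stated there) gives:

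- X→M: z = atanh(0.25) × √(261 × 0.85) = 0.2554 × 14.89 = 3.80; power Φ(3.80 − 1.96) = 0.967.
- M→Y, also allowing for the X–M correlation (R² = 0.15 + 0.0625): z = 0.2554 × √(261 × 0.7875) = 3.66; power 0.956.
- Joint: 0.967 × 0.956 = 0.92.

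Variants of the joint test give 0.92 to 0.94, and a Sobel test gives 0.74 to 0.77. The 0.80 is neither confirmed nor refuted, and the point does not depend on it.

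**2. Size of the borrowed path.** Inputs: n = 264, and a = b = 0.25 from the planning values. Let ρ be the correlation of the two mediators given communication. It is not in the article, so a range is shown. The true mediator has path b to the outcome and the inert one has path 0. With the true mediator omitted and communication adjusted for, the inert mediator's expected path is b × ρ:

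- ρ = 0.3: 0.25 × 0.3 = 0.075
- ρ = 0.4: 0.25 × 0.4 = 0.100
- ρ = 0.5: 0.25 × 0.5 = 0.125

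**3. Chance that the inert mediator is declared significant.** Single-level simulation, 4,000 replicates per cell; both of its paths must be significant at two-sided 0.05.

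| Assumed ρ | Rival omitted | Both in the model |
|---|---|---|
| 0 | 5% | 4–6% |
| 0.2 | 13% | 4–6% |
| 0.3 | 22% | 4–6% |
| 0.4 | 36% | 4–6% |
| 0.5 | 48% | 4–6% |
| 0.6 | 66% | 4–6% |

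Closed-form check at ρ = 0.3: partial correlation = 0.075 × √0.9375 / √0.996 = 0.073; z = 0.073 × √260 = 1.18; power for M→Y is 0.217. Multiplying by the X→M power without confounding (0.985) gives 0.21. The same formula gives 0.34 at ρ = 0.4 and 0.49 at ρ = 0.5, within about two percentage points of the table.

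**4. Do the lagged terms remove it?** Take a stationary within-person lagged process with stable between-person differences already removed. Assume autoregression 0.3, a = 0.25, true b = 0.30 (unstandardised), and adjustment for the lagged outcome and lagged communication. The inert mediator's standardised path is 0.10, 0.13 and 0.16 at residual ρ of 0.3, 0.4 and 0.5. It is 0.00 once both mediators are included. Random intercepts and autoregression remove stable differences, but not occasion-level correlation with an omitted mediator.

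**5. Power after the fix.** With both mediators in one model, use R² = 1 − 0.85 × 0.9375 × (1 − ρ²) for the M→Y path. Joint power for the true mediator is then 0.92, 0.91, 0.89, 0.86 and 0.81 at ρ = 0.2, 0.3, 0.4, 0.5 and 0.6. It does not fall below the planned 0.80 in this simplified setting.

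**The case against.** The strongest reply is that Aim 1 is worded as the overall fit of each model, not a head-to-head test. The theories also make different predictions: SCP concerns psychological adjustment through actor effects, while RI adds relationship adjustment through actor and partner effects. Both mediators are applied to both outcomes, with actor and partner paths estimated, so these patterns can be set side by side. Nothing in the article makes the theories mutually exclusive. This stands. A descriptive comparison remains possible, and it would be too strong to say that the purpose cannot be met. What it does not provide is a valid comparison of mechanisms for the shared outcome.

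Three stronger readings are tempting, and the article does not support them:

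- **That the models will be ranked by fit.** The Overview uses the indices only "as benchmarks for acceptable model fit". Mechanism is tested separately, through the indirect effects.
- **That support for SCP leads only to individual interventions.** The Discussion also allows couple-based interventions under SCP. The contrast it draws is one of focus.
- **That unequal reliability tilts the comparison.** "Mediators and outcomes will be treated as manifest variables in these models", and Table 1 gives alphas of 0.82–0.86 for the Impact of Events Scale against 0.86–0.91 for intimacy. The former read as subscale values, whereas the analysis uses a composite of both subscales. With two equal-variance subscales at 0.84 and intercorrelation r, composite reliability is 1 − 0.16/(1 + r). At an assumed r of 0.4 this is 0.886, against intimacy's mid-range 0.885, so the tilt disappears. Above that it reverses.

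Model size is a fair objection too. The questionnaire model already has 6 × 2 × 4 = 48 communication indicators plus 8 mediator and 8 outcome variables. A second mediator adds 8 more.

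**Conclusion.** The point holds as a mismatch between the stated purpose and the specified analysis. The article fixes an either/or mediator specification while promising a comparison, so this is not merely detail left to an unseen analysis plan. It bears chiefly on psychological distress, and less on relationship adjustment, which the hypotheses assign to RI alone.

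At the planning effect size, false support for an inert mediator is about 22–48% for mediator correlations of 0.3–0.5, against 4–6% with both modelled. These figures rest on an assumed correlation, vanish to the nominal level at zero in the single-level setting, and come from a simplified version of the planned models. They also ignore measurement error. A larger true path raises them: with b = 0.40 the corresponding range is 48–88%. In the EMA models avoidance and intrusive thoughts may enter as two variables, so there the issue is one mechanism per model rather than strictly one mediator.

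**What to change.** For both the questionnaire and the EMA data, add a parallel-mediator model with cognitive processing and intimacy together and a free residual correlation between them. Report the two specific indirect effects and a 95% confidence interval for their standardised difference (bootstrap for the questionnaire models, Monte Carlo for the multilevel ones). Do this for distress first and also for relationship adjustment. State that any SCP-versus-RI conclusion rests on that contrast. Keep the single-mediator models as the test of each theory alone.

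The cost is some analysis wording and one further model per outcome in each data set, with no new data. Confidence intervals for each specific indirect effect will be somewhat wider. The larger questionnaire model may be hard to estimate by maximum likelihood and may need the Bayesian estimation that the Overview already allows. The power figures above come from a simpler model and do not guarantee the same margin there.
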